## Introduction

### Background and rationale

Severe acute pancreatitis (SAP) is a common type of critical abdominal condition in clinical practice. Due to its rapid progression, SAP frequently prone to cause multiple organ dysfunction or even failure, resulting in high complication and mortality rates (1, 2). In patients with SAP who develop persistent organ failure, the mortality rate can be as high as 40% (3–5). Due to the changes in the body functions and circulation of patients with severe acute pancreatitis, the levels of inflammatory factors in their bodies will show a significant upward trend, thereby triggering a cascading reaction of inflammatory factors and subsequently leading to multiple organ dysfunction (6, 7). Previous studies (1, 6–8) have shown that in the early phase of SAP, the excessive release of inflammatory factors will further aggravate the severity of systemic inflammatory response syndrome and promotes the development of infected pancreatic necrosis. Therefore, inflammatory factors are significant factors influencing the onset and treatment of patients with SAP, and they are also important indicators reflecting the condition of patients with SAP (1, 9, 10).

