#### Plans for collection, laboratory evaluation and storage of biological specimens for genetic or molecular analysis in this trial/future use

Not applicable. This study will not involve the collection, storage, or analysis of biological samples.

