### Statistical methods

#### Statistical methods for primary and secondary outcomes

Continuous variables were tested for normality using the Kolmogorov–Smirnov test. Normally distributed data were presented as mean ± standard deviation (SD) and compared using the independent-samples *t*-test. Non-normally distributed variables were reported as median (interquartile range, IQR) and analyzed using the Mann–Whitney U test. Categorical variables were expressed as counts (percentages) and compared using the χ^2^ test or Fisher’s exact test, as appropriate.

In addition, the primary endpoint of this study was the mean lifespan of the hemodialysis filter during CRRT. Kaplan–Meier survival analysis was conducted to compare the cumulative probability of filter life over time, with the log-rank test applied for group comparison. To control for potential confounders (e.g., disease severity scores), multivariable linear regression and Cox proportional hazards models were used as sensitivity analyses.

Secondary outcomes included the changes in disease severity scores (SOFA and APACHE II), pancreatic enzymes (amylase, lipase) and inflammatory biomarkers (PCT, CRP, IL-6, IL-10, TNF-α) measured on Day 1 (baseline), day 3, day 5, and day 7 after randomization. To evaluate time-dependent trends and group differences, a repeated-measures analysis of variance (RM-ANOVA) was applied for normally distributed variables. Baseline disease severity characteristics, including etiology, CTSI/EPIC radiological scores, and the presence and grade of intra-abdominal hypertension, will be summarized descriptively and compared between groups using the χ^2^ test, Fisher’s exact test, or the Mann–Whitney U test, as appropriate. The assumption of sphericity was tested by Mauchly’s test, and when violated, the Greenhouse–Geisser correction was used to adjust degrees of freedom. Differences in change-from-baseline values (ΔSOFA, ΔAPACHE II, and Δbiomarker levels) between groups were analyzed using the independent-samples *t*-test or Mann–Whitney U test, as appropriate. Correlations between the changes in inflammatory markers and changes in severity scores were assessed using Spearman’s rank correlation coefficient.

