#### Methods in analysis to handle protocol non-adherence and any statistical methods to handle missing data

Because of the prospective design and short follow-up period of this trial, the occurrence of missing data in this study will be rare. Protocol deviations will be incorporated within an intention-to-treat framework, supported by a per-protocol analysis, while missing data will be handled primarily with mixed-effects models and, when necessary, multiple imputation with sensitivity checks.

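### Severity scores and biomarkers are assigned to RM-ANOVA and day-wise change tests that need complete visits, while the missing-data section names mixed-effects models and no rule covers death before day 7

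*Protocol article*

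**What the plan says.** Two sections of the protocol article bear on the same repeated measurements.

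- **Statistical methods for primary and secondary outcomes.** Disease severity scores, amylase, lipase and a list of inflammatory markers are "measured on Day 1 (baseline), day 3, day 5, and day 7 after randomization". For these, "a repeated-measures analysis of variance (RM-ANOVA) was applied for normally distributed variables". Sphericity is tested, and "when violated, the Greenhouse–Geisser correction was used to adjust degrees of freedom". A further sentence reads "Differences in change-from-baseline values (ΔSOFA, ΔAPACHE II, and Δbiomarker levels) between groups were analyzed using the independent-samples" t-test, with Mann–Whitney U as the alternative. No mixed model appears in this section.
- **Methods in analysis to handle protocol non-adherence and any statistical methods to handle missing data.** Here "the occurrence of missing data in this study will be rare", because the trial is prospective and follow-up is short. Then, within an intention-to-treat framework, "missing data will be handled primarily with mixed-effects models and, when necessary, multiple imputation with sensitivity checks".

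Three other places give context. Background and rationale says that in severe acute pancreatitis with persistent organ failure "the mortality rate can be as high as 40" per cent. Sample size estimation allows for about 10% dropout. Outcomes lists IL-8 and four coagulation parameters (aPTT, PT, fibrinogen, platelet count) among the day 1, 3, 5 and 7 measurements. The list in the statistical methods section includes none of these five.

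**The concern.** The article itself fixes two different approaches to the same data and does not say which one governs, so this is more than detail left to an analysis plan. If it stays open, the choice could be made after the data are seen.

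The methods named in the statistical section also fit this population poorly. A classical RM-ANOVA with a Greenhouse–Geisser correction needs every visit for each patient, and a change test on a given day needs that day's value. In severe acute pancreatitis under CRRT, some patients will die before day 7, and their absence is related to how ill they were. No section says what becomes of a SOFA score, an APACHE II score or a biomarker after death.

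RM-ANOVA is further restricted to normally distributed variables. Any skewed variable, which cytokines may well be, is left with separate day-wise rank tests and no analysis over time. The Discussion says that these outcomes will help to show an anti-inflammatory effect of nafamostat beyond anticoagulation. That reading would rest on whichever patients happened to have the necessary visits.

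**Working it through.** **1. The plan's own figure.** Inputs from Sample size estimation: difference 4 h, SD 8 h, two-sided α 0.05, power 80%.

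n per arm = 2 × (1.960 + 0.842)² × 8² / 4² = 2 × 7.85 × 4 = 62.8, so 63. With 10% dropout, 63 / 0.9 = 70. Both figures reproduce; the sample size is not in dispute.

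**2. Patients usable by each named method.** Let *d* be the share of patients dead or otherwise lost before day 7, and *q* the share of values missed at each of the three follow-up visits (days 3, 5, 7), taken as independent between visits. Day 1 is taken as complete.

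- RM-ANOVA (all visits needed): 70 × (1 − d) × (1 − q)³
- Day-7 change test (that day needed): 70 × (1 − d) × (1 − q)
- Mixed model (at least one follow-up value): at least about 70 × (1 − d) × (1 − q³). This is a lower bound, because patients lost after day 3 still contribute earlier visits.

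The 10% for *d* is the protocol's dropout allowance, which was set for the primary endpoint. Every value of *q*, and *d* = 0 or 20%, are assumptions.

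Central case, d = 10% and q = 5%:
- RM-ANOVA: 70 × 0.9 × 0.95³ = 63 × 0.857 = 54.0 (77% of 70)
- Day-7 test: 70 × 0.9 × 0.95 = 59.9

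| d | q | RM-ANOVA | Day-7 test | Mixed model |
|---|---|---|---|---|
| 0 | 5% | 60 | 66.5 | 70 |
| 10% | 0 | 63 | 63 | at least 63 |
| 10% | 5% | 54 | 60 | at least 63 |
| 20% | 5% | 48 | 53 | at least 56 |
| 20% | 10% | 41 | 50 | at least 56 |

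Independence of missed visits matters. If the same 5% of patients missed every follow-up visit, RM-ANOVA would keep 63 × 0.95 = 59.9 per arm in the central case, the same as the day-7 test.

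**3. Is missingness rare?** The missing-data section says so. Sample size estimation allows about 10% dropout. The mortality of up to 40% has no time point and refers to persistent organ failure, which under Eligibility criteria is only one of several alternative ways to qualify. It therefore cannot be turned into a day-7 figure. It does show that deaths during the measurement period cannot be assumed to be negligible.

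**4. Coverage of the outcomes.** The statistical section names nine variables: SOFA, APACHE II, amylase, lipase, PCT, CRP, IL-6, IL-10 and TNF-α. Outcomes adds IL-8, aPTT, PT, fibrinogen and platelet count. These five have no longitudinal analysis assigned.

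**The case against.** The strongest reply is that the two sections can be read together: RM-ANOVA is the base analysis, and mixed-effects models take over where visits are missing. The protocol nowhere says that patients are dropped. It lists both SPSS and R without tying either to this analysis. That reading is possible, and outright contradiction is a stronger word than the text requires. It does not remove the problem, because the article does not state that reading, and it would leave two analyses of the same data with neither designated. The loss of patients follows from the methods named, whichever software is used.

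It can also be said that the coagulation parameters fall under the general rule for continuous variables, and that the absence of IL-8 looks like an editorial slip. Both are fair. The coagulation parameters still have no analysis over time, and either omission is corrected by one line.

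Several stronger readings are tempting, and the document does not support them:

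- *Anyone who leaves the ICU before day 7 is lost.* The section on participant retention says that data after transfer to a general ward come from the electronic record.
- *Cytokines exist only where a clinician ordered them.* One section does say "This study will not involve the collection, storage, or analysis of biological samples", but its heading concerns specimens for genetic or molecular analysis or future use. Outcomes, Table 1 and the data collection section all schedule the biomarkers on fixed days. At most the specimen statements need a separate clarification.
- *Survivor-only analysis biases the arm comparison by a known amount.* That needs arm-specific death rates and a link between death and severity, and the protocol gives neither. A mixed model also would not remove such bias where death depends on a value never observed.
- *Baseline adjustment saves a definite share of the sample size.* The gain depends on a baseline-to-follow-up correlation that the document does not give, and no sample size rests on these outcomes.
- *The day-wise tests produce a specific number of false positives.* Such a count depends on which variables are included, and the labelling of secondary results is commonly left to the analysis plan.

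**Conclusion.** The point holds as an unresolved choice of analysis. The statistical section fixes methods that can use only patients with the necessary visits, the missing-data section puts mixed-effects models first, and neither is designated as governing. No rule covers death before day 7.

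At 10% dropout and an assumed 5% missed per visit, the RM-ANOVA would rest on about 54 of 70 patients per arm and the day-7 test on about 60, while a mixed model could use at least 63. Over the assumptions tabulated, the RM-ANOVA count runs from 41 to 63. These counts show how many patients each method can use. They are not estimates of bias. The expectation that missing data will be rare sits badly with the protocol's own dropout allowance and the mortality it cites.

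Only secondary outcomes are affected; the primary endpoint and the sample size are untouched. The change should be made because it is cheap and uses data already planned.

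**What to change.** 1. In the statistical methods section, replace RM-ANOVA and the day-wise change tests by one mixed model for repeated measures per variable, with baseline value, arm, day and arm-by-day as terms. Fit it in all randomised patients with data, and log-transform skewed biomarkers. This agrees with the missing-data section and gives skewed variables an analysis over time.
2. A mixed model does not define a score after death. Add an analysis of SOFA and APACHE II that ranks death before day 7 as the worst outcome, and report biomarkers as values while alive, alongside mortality by arm.
3. Add IL-8, aPTT, PT, fibrinogen and platelet count to the longitudinal analysis list.
4. Remove the statement that missing data will be rare.

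The cost is revised wording and a little more analysis work. No extra patients or measurements are needed.

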### Sample size estimation

The sample size was estimated based on the primary endpoint, which was average service life of the CRRT circuit lifespan or filter (hours). The assumed baseline value of approximately 30 h for the heparin group, together with the standard deviation used in this calculation, were derived from the pooled filter-lifespan data summarized in the network meta-analysis of CRRT anticoagulation strategies by Zhou et al. and the review of circuit-survival determinants by Tsujimoto and Fujii, which indicate that heparin-anticoagulated circuits typically survive on the order of 20–40 h with considerable between-study variability (17, 32). Because the standard deviation of filter lifespan varies significantly across studies, we deliberately chose a relatively conservative value (σ = 8 h) toward the higher end of the reported range, to avoid underestimating the required sample size. A minimum clinically important difference of 4 h (an approximately 13% relative extension over the assumed heparin baseline) was prespecified not purely on statistical grounds but because a gain of this magnitude would be expected to translate into approximately one fewer circuit change per patient over a typical treatment course, with corresponding reductions in nursing workload and blood loss associated with circuit priming and disconnection, as well as lower filter and consumable costs—benefits that are clinically and economically meaningful even though the absolute increase in hours is modest. Assuming a two-sided α level of 0.05 and a power (1–β) of 80%, the sample size was estimated using the approximate formula for comparing the means of two independent samples, resulting in a sample size of approximately 63 cases in each group. Taking into account the approximately 10% dropout rate, it is necessary to recruit 70 participants in each group.

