We designed a randomized controlled trial, with the average filter lifespan as the primary outcome measure, aiming to compare the anticoagulant effects of nafamostat mesylate and heparin during CRRT treatment in patients with SAP. Secondary outcomes, including changes in SOFA scores, APACHE II scores, pancreatic enzymes (amylase, lipase), and serial inflammatory biomarkers (PCT, CRP, IL-6, IL-8, IL-10, TNF-α), will help elucidate the anti-inflammatory effects of nafamostat mesylate beyond its anticoagulant role. To reduce methodological heterogeneity, the CRRT modality has been standardized as continuous venovenous hemodiafiltration (CVVHDF) for all enrolled participants because circuit lifespan may differ across CRRT modalities. In addition, concomitant hemoperfusion or other extracorporeal cytokine adsorption therapies will not be permitted during the intervention period to minimize confounding of both the primary endpoint and inflammatory biomarker analyses. In addition, we will also record the occurrence of adverse events and compare the safety of using nafamostat mesylate versus heparin anticoagulation in CRRT treatment for patients with SAP. This protocol focuses on circulating biomarker dynamics as a marker of the systemic inflammatory response; due to resource constraints, direct measurement of cytokine concentrations in the CRRT effluent was not incorporated into the current design, but represents a valuable direction for future mechanistic studies of the anti-inflammatory effect of nafamostat mesylate during blood purification (31). In summary, this study aims to compare the anticoagulant efficacy and safety differences between nafamostat mesylate and heparin in patients with SAP who receive CRRT. The results of this study are expected to provide guidance for the selection of anticoagulant drugs for critically ill patients with SAP who receive CRRT, and to clarify the optimal anticoagulation strategy for this population, thereby optimizing clinical practice for treating SAP patients.

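### The only named group-by-time analysis of the biomarkers depends on a normality test, and change is compared on what reads as the raw scale; for skewed markers this can cost power, by an amount the protocol does not fix

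*Protocol article*

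**What the plan says.** The relevant rules are in the protocol article, under Statistical methods for primary and secondary outcomes. The gate comes first: "Continuous variables were tested for normality using the Kolmogorov–Smirnov test". Variables that pass are compared by t-test. The others are summarised as median and interquartile range and compared by Mann–Whitney U.

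For the severity scores, enzymes and inflammatory markers measured on days 1, 3, 5 and 7, the method given for time trends and group differences is that "a repeated-measures analysis of variance (RM-ANOVA) was applied for normally distributed variables". No counterpart is named for variables that are not normal.

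Change is handled separately: "Differences in change-from-baseline values (ΔSOFA, ΔAPACHE II, and Δbiomarker levels) between groups were analyzed using the independent-samples" t-test or the Mann–Whitney U test. No logarithm, ratio or baseline covariate is mentioned, so the natural reading of Δ is follow-up minus baseline.

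Two other places bear on this. The section on non-adherence and missing data names mixed-effects models as the main way of handling missing values, without outcome, scale or model terms. The Discussion says that the secondary outcomes, including the serial biomarkers, "will help elucidate the anti-inflammatory effects of nafamostat mesylate beyond its anticoagulant role".

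**The concern.** A normality test decides which analysis each marker receives. Concentrations are positive and often right-skewed, so the markers that carry the anti-inflammatory question are those most likely to be sent away from the only trend analysis the section names. They would then rest on two-group tests of change, day by day.

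The scale of that change matters. If treatment lowers a marker by a fixed proportion, the raw fall is large in patients who start high and small in those who start low. Differences in baseline between patients then swamp the treatment contrast. A rank test does not cure this, because the ranks of raw differences are not the ranks of log differences.

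A less skewed marker brings a different problem: it may pass on one day and fail on another, so its method is chosen by the sample. What is at stake is the mechanistic conclusion, which could miss a real proportional effect or be reported inconsistently across markers and days.

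**Working it through.** **1. The plan's own figure.** Sample size estimation gives a difference of 4 h, SD 8 h, two-sided α 0.05 and power 80%. n = 2(1.96 + 0.842)² × 8² / 4² = 2 × 7.85 × 4 = 62.8, so 63 per group; 63 / 0.90 = 70. Both stated figures reproduce. They concern filter life only. The article gives no SD, correlation, effect or time course for any marker, so all that follows rests on assumed values.

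**2. Does a skewed marker fail the gate?** Simulated lognormal data; the article does not say which form of the Kolmogorov–Smirnov test is meant.

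| Log-scale SD | 63 levels: Lilliefors / uncorrected | 63 raw changes: Lilliefors / uncorrected |
|---|---|---|
| 0.5 | 76% / 21% | 36–65% / 3–12% |
| 0.8 | 99% / 73% | 82–94% / 37–59% |
| 1.2 | about 100% with Lilliefors | 99–100% / 90–93% |

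With raw changes pooled over both arms in the settings of step 4 where control levels halve, even the uncorrected test rejects in 95–100% of trials. Failure is near certain for strong skew. For mild skew it depends on the marker, the day and the version of the test.

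**3. Why raw change is inefficient, and when.** Take a patient with baseline B and a treatment that halves the follow-up level. The typical raw changes are:
- control level halves: −0.5B in control, −0.75B on treatment
- control level flat: 0 and −0.5B
- control level doubles: +B and 0

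On the log scale the contrast is ln 2 = 0.693 in all three cases. When both arms fall, both raw changes are negative multiples of B, and B itself varies by a factor of exp(1.2) = 3.3 per SD at log-SD 1.2. The time course in the control arm is therefore the main driver.

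**4. Power.** Assumed: 63 per arm, two-sided 0.05, one follow-up day, lognormal marker, true halving, baseline-to-follow-up correlation ρ of 0.5–0.7. For the t-test on log change a formula serves as a check: SD of log change = 1.2√(2(1 − ρ)), which is 1.20 at ρ = 0.5 and 0.93 at ρ = 0.7. SE = SD × √(2/63) = 0.214 and 0.166. Then 0.693/SE = 3.24 and 4.19, and power = Φ(3.24 − 1.96) = 90% and Φ(4.19 − 1.96) = 99%. Simulation at log-SD 1.2:

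| Control-arm median at follow-up | Mann–Whitney, raw change | t-test, log change |
|---|---|---|
| Halves | 40–52% | 89–99% |
| Falls about 30% | 56–74% | 90–99% |
| Flat | 70–88% | 89–98% |
| Doubles | 85–98% | 88–98% |

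At log-SD 0.8 the figures are 64–75% against about 100% if control levels halve, and 96–100% against about 100% if they are flat.

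**5. A smaller effect.** Set the effect so that log-scale ANCOVA has 80% power, at log-SD 0.8 and ρ = 0.5. Mann–Whitney on raw change then has 71% power if control levels double, 52% if flat, 41% if they fall 30%, 27% if they halve and 13% if they quarter. The t-test on log change stays at 65–69%, so raw change does slightly better than log change when levels double. Against ANCOVA the relative loss runs from 10% to 84%.

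**The case against.** Four stronger readings are tempting, and the documents support none of them.

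- *Skewed markers get no longitudinal analysis at all.* The missing-data section names mixed-effects models, and repeated day-3, 5 and 7 measurements are their natural use. It gives no outcome, scale or time-by-treatment term, so the gap is not closed. What stands is that the two sections are not reconciled.
- *Raw change is the only comparison left.* The general rule sends any non-normal continuous variable to Mann–Whitney, and the Outcomes section lists marker levels as well as changes. If day-specific levels are also to be compared, a log transform makes no difference to that test. With control levels halving and a true halving by treatment, its power is 89% and 87% at log-SD 1.2 (ρ = 0.5 and 0.7), which recovers most of the gap. The section names Δ for differences between groups, so the intention is unclear.
- *About half the power is lost.* That is one point in a wide range, governed by a time course the article does not state.
- *A true reduction will probably be reported as no difference.* Power of 64–75% or 70–88% under equally plausible assumptions does not bear this out.

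Skew itself is an assumption, since the article does not describe the marker distributions. Transformations and model terms are also often left to an analysis plan, which is not at hand, so their absence alone is no fault. The gate is different: it is a stated rule that a later plan would have to overturn.

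**Conclusion.** The point holds in this form. The article ties its one named group-by-time method for the biomarkers to a normality test, states no transformation for the comparison of changes, and leaves its mixed-effects models unconnected to either. Strongly skewed markers (log-SD about 0.8 or more) would usually fail, have no specified time-by-group analysis, and be compared on what reads as raw change. Mildly skewed ones could be treated differently by marker or day.

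The cost in power cannot be given as one figure. It is large if marker levels fall steeply in both arms, moderate if they are flat, and close to nil if they rise. These figures assume lognormal markers, a proportional effect and 63 per arm. The matter is worth correcting because the anti-inflammatory claim rests on these outcomes, but they are secondary.

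**What to change.** Under Statistical methods for primary and secondary outcomes, make these changes before any outcome data are seen:

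1. Prespecify log transformation of all concentration outcomes: PCT, CRP, IL-6, IL-8, IL-10, TNF-α, amylase and lipase. IL-8 is in the Outcomes section but missing from the marker list in the statistical section.
2. Drop the Kolmogorov–Smirnov gate for these outcomes.
3. Fit the same mixed-effects model to each one over days 3, 5 and 7, with treatment, day, their interaction and log baseline. State that this is the model meant in the missing-data section.
4. Report between-arm geometric-mean ratios with 95% confidence intervals at each day.

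The cost is wording only: no new patients, visits or measurements. Results become ratios, not absolute differences, and values below the detection limit need one fixed rule.

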### Outcomes

The primary endpoint of this study is the average service life of the CRRT circuit or filter. The functional lifespan of CRRT circuit begins when the extracorporeal circulation of blood starts and ends when the circuit is taken out of service by intensive care unit (ICU) staff (when the treatment goal is achieved, death occurs, or the upper limit of 72 h for filters). The reasons for ICU staff to stop the circuit operation included: (1) the transmembrane pressure on both sides of the circuit exceeded 300 mmHg, (2) visible blood clots hindered the blood flow within the machine, (3) the blood pump could not rotate due to blood clot blockage, (4) other (recorded by the bedside staff). The first three reasons are considered to be cases of circuit clotting. If the bedside staff recorded “other” or the reason for stopping the circuit was missing, adjudication is required. Two senior critical care specialists, who were not involved in the research, independently reviewed these cases and adjudicated the reasons for circuit discontinuation. In case of any disagreement, they resolved it through joint consultation. The outcome of the judgment may be one of three types (coagulated, non-coagulated or unknown condition). The circuit that is selectively discontinued due to reasons during the treatment process (such as transfer within the hospital) is regarded as “non-coagulated.”

The secondary endpoints of this study include: 1. SOFA and APACHE II scores were evaluated on days 1, 3, 5, and 7 after enrollment, and the changes from the baseline (ΔSOFA /ΔAPACHE II) were calculated to reflect the trend of disease progression; 2. Serum levels of pancreatic enzymes (amylase and lipase) and PCT, CRP, IL-6, IL-8, IL-10 and TNF-α were measured on days 1, 3, 5, and 7, and their changes from baseline were analyzed; 3. levels of coagulation parameters(include aPTT, PT, fibrinogen, platelet count) were assessed on specific days (day 1, 3, 5, and 7) together with their changes from baseline values; 4. time to successful initiation of enteral nutrition; 5. blood transfusion requirements(RBC, FFP, platelet units), 6. ICU length of stay and total hospitalization days; 7. Clinical outcomes (blood purification dependency rate, length of ventilator use and all-cause mortality at 28 days).

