All participants who received at least one dose of study anticoagulant were included in the safety set. The incidence of adverse events (AEs), serious adverse events (SAEs), and bleeding or coagulation complications were summarized using descriptive statistics and compared between groups with the chi-square test or Fisher’s exact test, as appropriate.

All statistical analyses were performed using SPSS version 26.0 (IBM Corp., Armonk, NY, United States) and R version 4.3.0 (R Foundation for Statistical Computing, Vienna, Austria). A two-sided *p*-value < 0.05 was considered statistically significant.

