#### Methods for additional analyses (e.g., subgroup analyses)

Subgroup analyses will assess whether treatment effects differ across predefined etiologies of acute pancreatitis (biliary, alcoholic, hypertriglyceridemia-related, post-ERCP, and other). Adjusted analyses will be performed using multivariable regression models to control for potential confounding factors.

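### One p < 0.05 rule covers every analysis, including an unranked set of marker tests from which an anti-inflammatory effect of nafamostat is to be inferred

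*Protocol article*

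**What the plan says.** The Outcomes section lists seven groups of secondary endpoints without ranking them. One group covers enzymes and inflammatory markers: "Serum levels of pancreatic enzymes (amylase and lipase) and PCT, CRP, IL-6, IL-8, IL-10 and TNF-α were measured on days 1, 3, 5, and 7", with changes from baseline to be analysed. SOFA, APACHE II and four coagulation parameters follow the same schedule.

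The section on statistical methods for primary and secondary outcomes applies repeated-measures ANOVA to those scores and markers that are normally distributed. It then adds: "Differences in change-from-baseline values (ΔSOFA, ΔAPACHE II, and Δbiomarker levels) between groups were analyzed using the independent-samples" t-test or the Mann–Whitney U test. Spearman correlations between marker changes and score changes come on top. Its list of inflammatory markers has five entries; IL-8, which the Outcomes section includes, is absent.

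The same section closes, directly after naming the software for all analyses, with: "A two-sided *p*-value < 0.05 was considered statistically significant". It makes no exception for secondary, correlation or subgroup analyses. The section on additional analyses states: "Subgroup analyses will assess whether treatment effects differ across predefined etiologies of acute pancreatitis".

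The Discussion says that the scores, enzymes and markers "will help elucidate the anti-inflammatory effects of nafamostat mesylate beyond its anticoagulant role". The strengths and limitations section says that this effect is inferred from trends in circulating markers, because clearance across the filter is not measured.

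**The concern.** A global p < 0.05 statement is a common closing line and would not by itself deserve comment. Here it sits beside an announced conclusion. The circulating markers are the evidence the article names for an anti-inflammatory effect, and the Discussion's wording takes that effect as existing. No marker, day or test is singled out to decide the matter. Followed as written, the plan lets one marker on one day, by either of two methods, count as statistically significant and be cited in support. The 5% in the significance rule would not then be the error rate of the conclusion drawn from the marker family.

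**Working it through.** **The plan's own error rate.** The sample size section sets alpha for filter life alone: "Assuming a two-sided α level of 0.05 and a power (1–β) of 80"%, difference 4 h, SD 8 h. The calculation is n = 2 × (1.960 + 0.842)² × 8² / 4² = 62.8, so 63 per group, and 63 / 0.9 = 70 with dropout. Both stated figures reproduce. This is one test of one endpoint, and the secondary tests do not change its error rate. The article states no error rate for the secondary family, so there is nothing further to reproduce.

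**Counting the marker tests.** Table 1 takes day 1 as baseline, which leaves changes at days 3, 5 and 7.
- Statistical section: PCT, CRP, IL-6, IL-10, TNF-α, so 5 × 3 = 15 tests.
- Outcomes section, which adds IL-8: 6 × 3 = 18 tests.

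Testing each day separately is inferred from the change values; the article does not say it outright.

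**Chance of at least one false positive, independent tests.** For k tests with no true effect, the chance in either direction is 1 − 0.95^k. The chance of a result favouring nafamostat uses one tail only and is 1 − 0.975^k.
- k = 15: 1 − 0.95^15 = 0.54; 1 − 0.975^15 = 0.32.
- k = 18: 1 − 0.95^18 = 0.60; 1 − 0.975^18 = 0.37.

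**Allowing for correlation.** Markers and days are correlated within patients. The documents give no correlations, so a common pairwise value r between normal test statistics is assumed, with critical value 1.96.

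| r | 15 tests, either direction | 15 tests, favouring nafamostat | 18 tests, either direction | 18 tests, favouring nafamostat |
|---|---|---|---|---|
| 0 | 0.54 | 0.32 | 0.60 | 0.37 |
| 0.3 | 0.46 | 0.23 | 0.51 | 0.26 |
| 0.5 | 0.36 | 0.18 | 0.40 | 0.20 |
| 0.8 | 0.20 | 0.10 | 0.22 | 0.11 |

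A more structured assumption for six markers (0.7 between days of one marker, 0.3 between markers) gives 0.46 in either direction and 0.24 favouring nafamostat, inside the range above.

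Against the nominal 0.025 for a false result favouring nafamostat, 0.10 to 0.37 is about 4 to 15 times as large. The repeated-measures ANOVA and the Spearman correlations are further looks at the same data and are not counted.

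**Effect of one overall test per marker.** With r from 0.8 to 0, six tests give 0.14 to 0.26 in either direction (1 − 0.95^6 = 0.26 if independent) and 0.07 to 0.14 favouring nafamostat. This lowers the chance but does not bring it to the nominal level, so a retained claim would also need control across markers.

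**The case against.** The strongest reply is that a condensed protocol article commonly leaves ranking and multiplicity to the analysis plan, which is not shown. The confirmatory structure is clear: one primary endpoint carries the sample size, and everything else is called secondary or additional. The Discussion's wording is supportive rather than confirmatory, and the limitations section concedes that the effect is inferred.

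Part of this stands. Silence on multiplicity alone would not be a finding. But the article does more than stay silent: it states a significance rule for all analyses and attaches a conclusion to an unranked family. An analysis plan that called these tests exploratory would contradict that text as it now reads.

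A reader might also infer several stronger things that the documents do not support.
- That a false anti-inflammatory finding for nafamostat is likely. Only one tail counts and the tests are correlated; the chance stays below one half throughout the range.
- That all secondary endpoints belong in the count. Fourteen repeated variables at three days plus nine single outcomes would make 14 × 3 + 9 = 51 tests, but coagulation values, lengths of stay and the like do not bear on an anti-inflammatory claim.
- That every marker is certainly tested twice. Repeated-measures ANOVA is limited to normally distributed variables.
- That the aetiology analysis adds five tests to this family. The article asks whether effects differ between aetiologies, which is an interaction question, and names no outcome for it.
- That the primary result is compromised. It is not.

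**Conclusion.** The point holds in limited form. As written, the significance rule applies to 15 or 18 marker comparisons with no ranking or exploratory status, and these comparisons are meant to inform a stated conclusion. With no true effect, the chance of at least one p < 0.05 among them is about 0.20 to 0.60, and of one favouring nafamostat about 0.10 to 0.37.

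These figures rest on two assumptions: separate tests at days 3, 5 and 7, and a common correlation between 0.8 and 0. The direction of the conclusion does not depend on the exact correlation, since even at 0.8 the chance favouring nafamostat is about four times nominal. What is affected is the secondary conclusion about inflammation, not the comparison of filter life. The plan should be changed, but its main test is sound in this respect.

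**What to change.** 1. In the statistical methods, limit claims of statistical significance to filter life. State that secondary, correlation and subgroup analyses are exploratory and are reported as estimates with 95% confidence intervals.
2. Replace the day-wise marker tests with one overall treatment comparison per marker over days 3 to 7.
3. Reword the anti-inflammatory statements in the Discussion and in the strengths and limitations section as hypothesis-generating. If the claim is to be kept as a finding, control the marker family, for example by Holm at 0.05 over one test per marker.
4. Reconcile the marker lists: IL-8 is an outcome in the Outcomes section but is missing from the list in the statistical section.

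The cost is a few sentences, with no new data and no more patients. The small downside is that isolated secondary p-values below 0.05 can no longer be presented as significant findings.
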